**Methods/Design:**

We will perform a multicentre, blinded, randomized, controlled trial comprising 140 women with gynecologic malignancies undergoing pelvic lymphadenectomy. Women will be randomly allocated to Tachosil® application or no application. Primary outcome is efficacy, defined as lymphocele CTCAE 4.03 grade ≥2 within four weeks after surgery. Secondary outcomes are asymptomatic lymphocele verified by ultrasound, medical or surgical intervention. Assuming a two-sided 5% significance level, a power of 80%, and a drop out rate of 10%, a sample size of 68 patients per group was calculated to detect a 66% absolute decrease in symptomatic lymphoceles.

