### Outcome variables

2.8.1. The incidence of symptomatic pelvic lymphoceles CTCAE 4.03 grade ≥2 within 4 weeks after surgery in women undergoing open or laparoscopic pelvic lymphadenectomy for cervical or endometrial cancer (primary outcome variable).

2.8.2. The incidence of sonographically detected pelvic lymphoceles of at least 2 cm in the largest diameter 4 weeks after surgery in women undergoing open or laparoscopic pelvic lymphadenectomy for cervical and endometrial cancer with and without the application of Tachosil® during surgery (secondary outcome variable).

2.8.3. The rate and type of medical interventions for clinically symptomatic pelvic lymphoceles such as analgesics and/or lymphocele puncture and drainage (secondary outcome variable).

2.8.4. The length of hospital stay (secondary outcome variable).

2.8.5. The rate of predefined complications, ie abscess in the pelvis, fever >38°C on at least two occasions >24 hrs apart, leg swelling, local pelvic bleeding complications necessitating a surgical intervention (secondary outcome variable).

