### Statistical analysis

A power calculation demonstrated that, with a sample size of 70 per group, a two-arm study has a power of 80% to detect a 66% absolute difference in treatment efficacy at a significance level of 0.05 regarding the primary outcome parameter, ie symptomatic lymphoceles CTCAE 4.03 grade ≥2. This calculation was based on published data by Tinelli et al. observing a rate of 32% of symptomatic lymphoceles in the placebo group and 10% in the Tachosil® group [5]. Assuming a 10% drop out-rate, 140 women will be randomized. The chi-square test will used for comparisons of frequencies and cross-tabulations. One Way ANOVA on ranks will be used on means. Descriptive statistics (means, standard deviations, and ranges) will be used for demographic data. Bonferroni’s correction will be used for multiple comparisons of secondary outcomes.

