### Risk benefit assessment

The expected rate of intraoperative and postoperative complications following the study-based additional intervention, i.e. application of two patches of Tachosil®, will be minimal based on published studies [4–9]. For example, Simonato et al. and Tinelli et al. reported no complication associated with the use of Tachosil® patches [4, 5]. However, local infectious complications, pain, and abscess cannot be ruled out. A patient insurance for all participating women will be contracted covering all eventual harm caused by study participation. Also, the duration of the surgical intervention will not be increased due to the study intervention in a relevant manner [4, 5].

Women recruited for this study may eventually benefit from participating since a previous randomized trial in men undergoing pelvic lymphadenectomy has resulted in a significant benefit of Tachosil® regarding occurrence of lymphoceles and lymphocele drainage volume. Also, the number of medical interventions such as percutaneous punctures may be reduced in the intervention group.

The putative findings of our study could help to modify one step of the surgical technique of pelvic lymphadenectomy, one of the most common gynecologic oncology surgical procedures.

The present study has been approved the Ethics Committee of the Medical University of Vienna, Austria by September 9^th^, 2011 (EC no.: 740/2011), of the Charles University in Prague, Czech Republic by March 15^th^, 2012 (EC no.: cj459/12), and of the Marienhospital Bochum, Germany by August 24^th^, 2012 (EC no.: 4299–12 FF).

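### Bonferroni's correction takes in the predefined complications (2.8.5) without exemption, so an excess of complications in the patch arm is tested at 0.0125 instead of 0.05

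*Protocol article*

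**What the plan says.** Three places in the protocol article bear on this.

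- **Statistical analysis.** Frequencies are compared by chi-square: "The chi-square test will used for comparisons of frequencies and cross-tabulations". For multiplicity, Bonferroni's "correction will be used for multiple comparisons of secondary outcomes". No outcome is exempted and the number of comparisons is not given. The 0.05 level is stated for the primary outcome only: "at a significance level of 0.05 regarding the primary outcome parameter". The abstract makes it two-sided.
- **Outcome variables.** Four outcomes are labelled secondary: sonographic lymphocele (2.8.2), interventions (2.8.3), length of stay (2.8.4) and complications (2.8.5). The last reads "The rate of predefined complications, ie abscess in the pelvis, fever >38°C on at least two occasions >24 hrs apart", then adds leg swelling, and closes with "local pelvic bleeding complications necessitating a surgical intervention (secondary outcome variable").
- **Risk benefit assessment.** Few complications are expected from the patch, but the section goes on: "However, local infectious complications, pain, and abscess cannot be ruled out".

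The article describes no other comparison of complications and no separate level for harm.

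**The concern.** Bonferroni's correction buys protection against false positive findings at the price of more false negatives. That is a sensible trade for secondary claims of benefit. For a possible harm of a preventive product, the missed signal is the costlier error, and the rule as written makes it more likely.

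This is more than a detail left for an analysis plan. The article states a rule and attaches the label that brings complications under it. An analysis plan that followed the article would carry the rule forward. At stake is how the trial reports an excess of, say, pelvic abscess: a difference with a p-value between 0.0125 and 0.05 would be declared non-significant only because efficacy outcomes share its family.

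**Working it through.** **1. The plan's own sample size.** Inputs from Statistical analysis and the abstract: 32% versus 10%, two-sided 0.05, power 80%, dropout 10%. The usual two-proportion formula gives 53 per group, or 62 with continuity correction. Then 62/0.9 = 68.9, rounded up to 69, which is within two of both the 70 in Statistical analysis and the 68 in the abstract. The design figure reproduces.

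**2. Evaluable women.** 140 randomised is 70 per arm; 70 × 0.9 = 63.

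**3. Level for complications.** Family of 2.8.2 to 2.8.5: 0.05/4 = 0.0125. This assumes that the two-sided 0.05 of the primary analysis is the level being divided.

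**4. Events needed (no assumed rates).** With x control and y patch-arm events and 63 per arm, the uncorrected chi-square is

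X² = 126 (y − x)² / [(x + y)(126 − x − y)],

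with critical values 3.841 at 0.05 and 6.239 at 0.0125. For x = 0 it reduces to 126y/(126 − y):

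- y = 3: 378/123 = 3.07, not significant at either level
- y = 4: 504/122 = 4.13 (p = 0.042), significant at 0.05
- y = 5: 630/121 = 5.21 (p = 0.023), significant at 0.05 only
- y = 6: 756/120 = 6.30 (p = 0.012), significant at 0.0125

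So 6 events are needed instead of 4. With one control event, the requirement rises from 7 to 9; for example, 8 versus 1 gives 126 × 49/(9 × 117) = 5.86 (p = 0.015), which fails under the correction.

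**5. Power.** The document gives no complication rates, so these are assumed and shown as a range. Exact power is the sum, over all pairs (x, y), of Bin(x; 63, control rate) × Bin(y; 63, patch rate) wherever X² reaches the critical value.

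| Control vs patch (assumed) | Power at 0.05 | Power at 0.0125 |
|---|---|---|
| 5% vs 10% | 18% | 6% |
| 5% vs 15% | 48% | 24% |
| 5% vs 20% | 75% | 53% |
| 10% vs 30% | 82% | 64% |

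A normal approximation agrees closely: 73% and 52% for 5% versus 20%, and 46% and 26% for 5% versus 15%.

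**The case against.** **2.8.5 is not a pure harm outcome.** The Background defines symptomatic lymphocele by pelvic pain, abscess, fever or leg edema with a verified lymphocele. Abscess, fever and leg swelling in 2.8.5 overlap with that. Bleeding might also fall, since the product is licensed to support hemostasis. Removing 2.8.5 from the family altogether would allow an uncorrected claim of benefit. This objection stands and shapes the fix.

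**The correction may have been meant for something else.** The sentence follows those on chi-square and ANOVA on ranks, and the aims compare three centers and several surgical devices. It could be meant for such multi-group comparisons only, which would leave a single patch-versus-control test of 2.8.5 uncorrected. That is possible, but the sentence speaks of secondary outcomes without limit, so the broad reading is the natural one. The ambiguity is itself a reason to state the rule.

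**Sample size is the larger limit.** For 5% versus 10%, power is 18% even at 0.05. True, and the reason why estimates with intervals matter more here than tests.

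**Nothing says that non-significance will be read as safety.** Also true. The correction does not stop anyone from reporting counts and differences by arm, and a misleading reading is a risk, not something the article announces.

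**Conclusion.** The point holds in a limited form. A stated rule and a stated label together hold an excess of complications to 0.0125 instead of 0.05. Under the assumed rates of 5% versus 20% and 5% versus 15%, this costs 22 and 24 percentage points of power (75 − 53 and 48 − 24). It also raises the events needed against 0/63 from 4 to 6. The primary analysis is untouched.

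The size rests on 63 evaluable women per arm, a family of four, an uncorrected chi-square and assumed complication rates. The event counts need the first three but no assumed rates.

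Two stronger readings are tempting but not supported:

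- **That 2.8.5 is the only outcome able to show harm.** It is the only one dedicated to complications. Interventions and length of stay could worsen too, although both are also secondary. The two-sided primary comparison, at an uncorrected 0.05, counts pain, abscess and fever when a lymphocele is present.
- **That the level is far below 0.0125.** Adding aims 2.1.4 to 2.1.9, each for total and symptomatic lymphocele, gives 4 + 12 = 16 comparisons and 0.05/16. As worded, however, those aims contrast centers, tumor types, devices, nodal status, node counts and surgical approach, not patch with control. The document gives no count that supports the smaller level.

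**What to change.** Add a short statement to Statistical analysis:

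- An excess of any 2.8.5 component in the patch arm is assessed without Bonferroni correction. Each component is reported by arm with the risk difference and an unadjusted 95% confidence interval.
- Non-significance is not read as absence of harm.
- Any claim that the patch reduces 2.8.5 stays in the corrected family with the other secondary efficacy outcomes.

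This changes no sample size, procedure or data collection. The cost is a somewhat higher chance of a false safety signal. A two-sided 0.05 test nominally flags a false excess in the patch arm 2.5% of the time, so over four components the chance is at most about 4 × 2.5% = 10%. That is tolerable if such signals are read descriptively, alongside their intervals.

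### Single-step Bonferroni for the secondary outcomes is valid but needlessly conservative; Holm's step-down procedure gives the same familywise protection and never rejects less

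*Protocol article*

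**What the plan says.** Under Statistical analysis, the protocol article names Bonferroni and states that this "correction will be used for multiple comparisons of secondary outcomes". It mentions no step-down version and gives no reason for the single-step form. For comparing groups it names tests only (chi-square for frequencies, ANOVA on ranks for means); no simultaneous confidence intervals are planned.

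The only significance level is stated "at a significance level of 0.05 regarding the primary outcome parameter". The Abstract adds that it is two-sided.

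Two lists could form the family. Outcome variables has four secondary items (2.8.2 to 2.8.5): sonographic lymphocele, interventions, hospital stay and predefined complications. The interventions item reads "The rate and type of medical interventions for clinically symptomatic pelvic lymphoceles such as analgesics and/or lymphocele puncture and drainage". Aim of the study has eight secondary aims (2.1.2 to 2.1.9), six of which (2.1.4 to 2.1.9) compare centres, cancer types, devices, nodal status, node counts and surgical approach rather than treatment arms.

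**The concern.** Single-step Bonferroni holds every one of m tests to 0.05/m, even after others have been rejected. Part of the permitted 5% error then goes unused whenever some effects are real. That bears on this trial because one secondary outcome, sonographic lymphocele, may show a large effect and be rejected early, while the outcomes closer to the patient, such as interventions, are weakly powered. At stake is some power on those secondary comparisons. The primary result is not involved.

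**Working it through.** **1. Thresholds, for any family.** Holm orders the p-values and compares them in turn with 0.05/m, 0.05/(m−1), …, 0.05, stopping at the first failure. No threshold is below Bonferroni's 0.05/m, so Holm rejects whatever Bonferroni rejects. It rests on the same inequality, so it needs no assumption about dependence.

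- m = 4: Bonferroni 0.0125 throughout; Holm 0.0125, 0.0167, 0.025, 0.05.
- m = 8: Bonferroni 0.00625 throughout; Holm starts 0.00625, 0.00714, …

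With m = 8 a first rejection relaxes the next threshold only slightly, so the size of the family matters. The first threshold is the same in both methods, so the chance of at least one rejection is identical.

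**2. Number per arm.** No figure is attached to the Bonferroni sentence, so the plan's sample size is reproduced first. For 32% versus 10%, two-sided 0.05 and 80% power, the continuity-corrected formula gives 62 per group; 62/0.9 = 68.9, so 69, or 138 in total, close to the planned 140. Without the correction it gives 53 per group (53/0.9 = 58.9, so 59), which does not match. Evaluable per arm: 140 × 0.9 / 2 = 63.

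**3. General simulation.** 200,000 runs per setting, family level 0.05 (assumed for the secondary outcomes), independent tests; each real effect is assumed to have 80% power unadjusted. Mean power per real effect, Bonferroni to Holm:

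| Family size | One effect real | Half real | All real |
|---|---|---|---|
| 4 | 62.1% to 62.3% | 61.9% to 64.5% | 62.0% to 72.7% |
| 8 | 52.6% to 52.7% | 52.8% to 56.0% | 52.7% to 64.4% |

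Gains at correlation 0.5 are similar. Holm's largest familywise error was 0.049, and its rejections contained Bonferroni's in every run.

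**4. Scenarios with the article's rates.** 63 per arm, correlated outcomes, Pearson tests for binary outcomes and a z-test for stay. Inputs:

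- Sonographic lymphocele 51.7% versus 19.2% (Discussion, retrospective comparison with historical controls).
- Interventions 4/30 = 13.3% versus 1/30 = 3.3% (Background; punctures only, in men with prostate cancer).
- Stay shorter by 0.35 SD, and complications 15% versus 8% (both assumed).

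| Scenario | Interventions | Stay |
|---|---|---|
| Three outcomes (without complications) | 38% to 46% | 33% to 43% |
| Four outcomes | 30% to 39–40% | 30% to 36–37% |
| Four outcomes plus four true nulls (m = 8) | 20.2% to 22.0% | 22.1% to 23.4% |

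With four outcomes, complications also gain (about 9% to 14–15%), and sonographic lymphocele gains 1 to 2 points. Correlations from 0 to 0.6 make little difference.

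**5. Less favourable rates.**

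- The Background and Discussion print 9/28 as 57.7% for the controls of the earlier randomized trial in women, but 9/28 = 32.1%. At 32.1% versus 23.3%, the gains on interventions and stay fall to about 2 to 4 points.
- The Background also gives up to 11% asymptomatic lymphoceles and 2% needing intervention in women. With those as control rates and an assumed two-thirds reduction (m = 4), sonographic power is about 15%, and Holm adds about 2 points there, 0.1 on interventions and 0.8 on stay.

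**6. Unused error.** With one true effect, simulated familywise error on the remaining nulls was 3.0–3.6% for Bonferroni and 4.2–5.1% for Holm. The 5.1% is within simulation error (about 0.2 points) of the nominal 5%.

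**The case against.** Bonferroni is conventional and correct, nothing in the article is misstated here, and Holm's dominance would apply to any trial that writes Bonferroni. That stands, and it is why this is an optional refinement and not a fault. It does not remove the point: the article fixes the procedure, and a better one with the same guarantee costs almost nothing.

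A reader might infer that substantial power is lost for nothing whatever the family. The documents do not support that. The dominance holds for every family; the size of the loss does not. The largest gains need a small family and a large sonographic effect. The three-outcome family matches neither of the article's lists, the intervention rates come from men and omit analgesics, and two inputs are assumptions. Bonferroni also has one real advantage, simple simultaneous intervals, although this plan does not use it.

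A reader might also infer that interventions and hospital stay bear the whole loss. They do not: with four outcomes, complications gain a comparable amount, and sonographic lymphocele gains slightly.

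**Conclusion.** The point holds as a minor improvement. Single-step Bonferroni controls the error rate but gives up some power that Holm would keep at the same familywise 5%. For this trial the gain is about 0 to 10 percentage points per secondary outcome, with the upper end in favourable scenarios only; the general simulation reaches about 12 points (64.4 − 52.7 = 11.7) if every one of eight effects is real. It is near nil with one real effect, and always nil for the chance of at least one rejection.

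That Holm never does worse needs no assumption. The size rests on 63 evaluable women per arm, a 5% family level for the secondary outcomes (the article states 0.05 for the primary outcome only), and effect sizes that are borrowed or assumed. It would be wrong to read this as inflated type I error or as a threat to the primary analysis.

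**What to change.** In Statistical analysis, replace Bonferroni's correction with the Holm step-down procedure at a familywise two-sided 5% for the secondary outcomes, and report Holm-adjusted p-values. Make the change before unblinding, so that it cannot look like a choice made after seeing the results.

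The cost is a change of wording and one software option; no extra patients, data or assumptions are needed. Simultaneous intervals that match Holm are less simple than Bonferroni's. If unadjusted 95% intervals are shown beside the adjusted p-values, label them as unadjusted, because such an interval can exclude no effect while the adjusted p-value is not significant.

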### Risk benefit assessment

The expected rate of intraoperative and postoperative complications following the study-based additional intervention, i.e. application of two patches of Tachosil®, will be minimal based on published studies [4–9]. For example, Simonato et al. and Tinelli et al. reported no complication associated with the use of Tachosil® patches [4, 5]. However, local infectious complications, pain, and abscess cannot be ruled out. A patient insurance for all participating women will be contracted covering all eventual harm caused by study participation. Also, the duration of the surgical intervention will not be increased due to the study intervention in a relevant manner [4, 5].

Women recruited for this study may eventually benefit from participating since a previous randomized trial in men undergoing pelvic lymphadenectomy has resulted in a significant benefit of Tachosil® regarding occurrence of lymphoceles and lymphocele drainage volume. Also, the number of medical interventions such as percutaneous punctures may be reduced in the intervention group.

The putative findings of our study could help to modify one step of the surgical technique of pelvic lymphadenectomy, one of the most common gynecologic oncology surgical procedures.

The present study has been approved the Ethics Committee of the Medical University of Vienna, Austria by September 9^th^, 2011 (EC no.: 740/2011), of the Charles University in Prague, Czech Republic by March 15^th^, 2012 (EC no.: cj459/12), and of the Marienhospital Bochum, Germany by August 24^th^, 2012 (EC no.: 4299–12 FF).

### Follow-up

All women will undergo a gynecologic examination and a transvaginal and transabdominal ultrasound examination at the time of discharge of the hospital, performed by a physician experienced in transvaginal and transabdominal ultrasound examinations, who has not participated in the original surgical procedure and is blinded to the treatment allocation. All women will be scheduled for a follow-up visit 4 weeks after surgery including a gynecologic examination and a transvaginal and transabdominal ultrasound examination, performed by a physician experienced in transvaginal and transabdominal ultrasound examinations, who has not participated in the original surgical procedure and is blinded to the treatment allocation.

### Data management and safety

Patients will be pseudo-anonymized for protection of data privacy. At the time of inclusion, a code based on initial of given name and surname and their date of birth will be assigned to every patient. The code will only be used for data entry in the database, as the patient’s full name is not documented in the same database, where clinical information is collected and stored. During the clinical routine and follow-up visits patient information is documented on study documents, where both, patient’s full name and patient’s code, have to be documented. Only the principal investigators (CT, DC, and AR) will have access to study data.

## Discussion

The present randomized, controlled trial aims to evaluate the efficacy of Tachosil® in the prevention of symptomatic lymphoceles after pelvic lymphadenectomy in gynaecological malignancies. This is a clinical relevant topic as along with lymphedema, symptomatic lymphoceles are the major complication after pelvic lymphadenectomy. Recently, a study in patients with endometrial cancer described a prevalence of 23% for lymphedema after pelvic lymphadenectomy [10]. Due to the importance of this topic a prospective trial led by the Gynecologic Oncology Group has been released (GOG 244, GOG LEG study, The Lymphedema and Gynecologic Cancer Study).

In contrast to lymphedema, which is rather a chronic problem after pelvic lymphadenectomy, lymphoceles are more of an acute complication. The prevalence of lymphoceles after pelvic lymphadenectomy provided in the literature varies quite substantially between 11-63% [4, 5]. Symptomatic lymphoceles seem to occur in about 32% of patients undergoing pelvic lymphadenectomy [5]. This variation might be caused by numerous factors: the time interval between surgery and follow-up visit for lymphoceles as most of the small lymphoceles will spontaneously regress over time, rather small study populations in the majority of trials, the extent of lymphadenectomy, the use of new energy sources [5, 11]. Another interesting factor possibly influencing the rate of lymphoceles after pelvic lymphadenectomy might be the surgical approach. One study revealed a postoperative lymphocele rate of 15.4% and 1.4% in women after laparoscopic and after open pelvic lymphadenectomy, respectively [12]. Of note, this study retrospectively compared 138 women, who underwent systematic laparoscopic pelvic lymphadenectomy, to 123 historical control subjects, who underwent systematic pelvic lymphadenectomy via an open approach. Due to the design, this study has to be interpreted with caution [12]. In the present study, we aim to prospectively describe the lymphocele rates following open compared to laparoscopic systematic pelvic lymphadenectomy in women with gynecological malignancy.

The value of Tachosil® in the prevention of lymphoceles after pelvic lymphadenectomy in women has already been studied in two clinical trials [5, 13]. In a retrospective matched case–control study, a cohort of 26 patients receiving Tachosil® after laparoscopic pelvic lymphadenectomy was compared to a historical cohort of 29 women without Tachosil® after laparoscopic pelvic lymphadenectomy. The study described a significant difference in the prevalence of total lymphoceles (19.2% of patients in the Tachosil® group vs. 51.7% in the historical control group) and a non-significant difference of symptomatic lymphoceles (7.6% of patients in the Tachosil® group vs. 17.2% in the historical control group). Of note, this was not a prospective trial with a limited number of patients [13]. The second study was a prospective randomized controlled trial comprising 58 women with endometrial cancer after undergoing pelvic lymphadenectomy with or without Tachosil® [5]. This trial observed, that Tachosil® seems effective to reduce the rate of lymphoceles after pelvic lymphadenectomy [5]. 7/30 (23.3%) women in the treatment group compared to 9/28 (57.7%) women in the control group developed asymptomatic lymphoceles (p < 0.05) [5]. No significant differences between the two groups were observed in the development of symptomatic lymphoceles or the rate of interventions [5]. This may be attributable to the small sample size of this study.

As symptomatic lymphoceles are more relevant for the patient, it seems clinically more important to evaluate the impact of Tachosil® on the rate of symptomatic lymphoceles after pelvic lymphadenectomy. Therefore, we intend to perform a multi center randomized clinical trial assessing the efficacy of a collagen-fibrin patch for preventing symptomatic lymphoceles in women undergoing pelvic lymphadenectomy for gynecologic malignancies, ie cervical and endometrial cancer. We hypothesize that based on the data of *Simonato et al.* and *Tinelli et al.*, the application of a collagen-fibrin patch (Tachosil®) will reduce the number of symptomatic pelvic lymphoceles by at least 66%.

